### Objectives {7}

The primary objective of our parallel randomized controlled trial is to evaluate the efficacy and acceptability of an intensive 3-week VRCET-based psychotherapy (VRCET +), i.e., VRCET + MFCT, in reducing self-reported cocaine craving in inpatients hospitalized for CUD, by comparing its immediate post-treatment effects to the ones of a traditional PCET.

The secondary objectives of our trial will be:To evaluate the effects after 2 weeks of treatment (V1; VRCET vs. CET), post-treatment (V2; VRCET + vs. PCET), and 1-month post-treatment (V3; VRCET + vs. PCET) on urinary, physiological, and self-reported measures of cocaine use-related measures (abstinence, risk of relapse, self-efficacy to cope with craving, emotional dysregulation, and identification to dysfunctional thoughts)To evaluate the effects of VRE to cocaine cues on cue-specific cocaine craving-related measures (cocaine craving, emotional states, self-efficacy to cope with craving) and cue-exposure specific measures (sense of presence, ecological validity, cybersickness) compared to a traditional non-VR pictures-based cue-exposure (PCE).To evaluate the cognitive, behavioral, or emotional factors (cocaine craving, self-efficacy to cope with craving, dysfunctional thoughts, cocaine use and emotional dysregulation) mediating the efficacy of VRCET + in decreasing self-reported cocaine craving.To evaluate the acceptability of (i) our intensive VRCET as a stand-alone (V1) or add-on (V2; VRCET +) therapeutic intervention via client satisfaction towards psychotherapeutic services measures and (ii) VRE, as a cue-exposure paradigm via cybersickness self-reported measures.

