### Outcomes {12}

Our primary outcome will consist in the decrease of the self-reported cocaine craving as assessed with the French Craving Experience Questionnaire (CEQ; [53, 54]. The CEQ is an 11-item retrospective measure of cocaine craving containing two subscales: craving strength (CEQ-S) and frequency (CEQ-F). Each item is completed by the participants on a 10-point scale, from “not at all” (1) to “extremely” (10). The CEQ has shown good psychometric properties [54]. Means of CEQ-S and CEQ-F total scores will be analyzed. Finally, the CEQ will be administered before treatment (V0), after 2 weeks of treatment (V1; VRCET vs. PCET), post-treatment (V2; VRCET + vs. PCET), and 1-month post-treatment (V3; VRCET + vs. CET). The CEQ-S will be administrated immediately after a 7-min VRE to a cocaine-related situation, with a similar scenario to the CET situation 5 (Table 1) but across different virtual environments, avatars, and item appearances (Fig. 9). The CEQ-F will be administrated retrospectively, targeting the last 14-day period. (Table 4)

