Secondary outcomes will consist of:Assessing the effects after 2 weeks of treatment (V1; VRCET vs. PCET), post-treatment (V2; VRCET + vs. PCET), and 1-month post-treatment (V3; VRCET + vs. PCET) on cocaine use-related measures (abstinence, risk of relapse, emotional dysregulation, and dysfunctional thoughts) measured via urinary samples and self-reported questionnaires.Negative cocaine urine test strips will be used for objectively support participant self-reports of cocaine abstinence [55].Timeline Followback (TLFB) mean total scores will be used for subjectively assess participants cocaine abstinence in within the last 21 days, ranging from 0 (“none”) to 100 (“total abstinence”; [56]).Advance Warning of Relapse (AWARE) mean total scores will be used to subjectively assess the decrease of participants risk of cocaine use relapse within the next 2 months, ranging from 25 (11 to 37%-risk) to 193 (53 to + 95%-risk; [57]).The Difficulties in Emotion Regulation Scale (DERS) mean total scores will be used to subjectively assess the decrease of participant emotional dysregulation, ranging from 36 (“Almost never”) to 180 (“Almost always”; [58]).The Questionnaire of Core Beliefs related to Drug Use and Craving (QCBDU) – Beliefs Related to Addiction mean total scores will be used to subjectively assess the decrease of participant identification to dysfunctional thoughts related to CUD, ranging from 0 (“Strongly disagree”) to 72 (“Strongly agree”; [59]).Assessing at V0 the effects of VRCE to cocaine cues on cue-specific cocaine craving-related subjective (cocaine craving, emotional states, self-efficacy to cope with craving), physiological reactivity (blood pulse, skin temperature and conductance), and cue-exposure specific measures (sense of presence and ecological validity), as compared with PCE. The physiological measures and the self-reported measures will be administered, respectively, during and immediately after a 7-min VRE or PCE to a cocaine-related situation, with similar scenario to the CET situation 5 (Table 1), but with different virtual environments, avatar, and item appearances (Fig. 9).

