The dispersion of blood pulse, skin temperature, and conductance signals will be used through PLUX Biosignals physiological captors (medical device certification: ISO 13485) to assess the cue-specific reactivity in VRCE compared to PCE.The CEQ-S mean total scores will be used to subjectively assess cocaine craving intensity in participants exposed to VRCE compared to PCE; items range from 11 (“not at all”) to 110 (“extremely”; [54]).The Brief Mood Introspection Scale (BMIS) mean total scores will be used to subjectively assess negative and positive emotional states in participants exposed to VRCE compared to PCE. Items range from 0 (“definitely do not feel”) to 21 (“definitely feel”; negative emotions) or 27 (positive emotions; [60]).The Drug Taking Confidence Questionnaire – 8 (DTCQ-8) mean total scores will be used to subjectively assess the self-efficacy to cope with cocaine craving in participants exposed to VRCE compared with PCE; items range from 0 (“not at all confident”) to 800 (“very confident”; [61]).The Spatial Presence for Immersive Environments (SPIE) – Spatial Presence subscale mean total scores will be used to subjectively assess the sense of presence experienced by participants exposed to VRCE compared with PCE; items range from 4 (“strongly disagree”) to 20 (“strongly agree”; [62].The Spatial Presence for Immersive Environments (SPIE) – Realism subscale mean total scores will be used to subjectively assess the increased sense of reality experienced by participants exposed to VRCE compared with PCE, ranging from 4 (“strongly disagree”) to 15 (“strongly agree”; [62]).The Independent Television Commission Sense of Presence Inventory (ITC-SOPI) – Ecological Validity subscale mean total scores will be used to subjectively assess the increased sense of ecological validity experienced by participants exposed to VRCE compared to PCE; items range from 5 (“strongly disagree”) to 25 (“strongly agree”; [25]).Assessing the cognitive, behavioral, or emotional factors (cocaine craving, dysfunctional thoughts, cocaine use, and emotional dysregulation) mediating the efficacy of VRCET+ in decreasing self-reported cocaine craving. The CEQ – F, QCBDU, TLFB, and DERS mean total scores will be used to subjectively assess, as aforementioned, cocaine craving frequency (last 14 days), dysfunctional thoughts regarding CUD, cocaine abstinence (last 21 days), and difficulties in emotion regulation.Assessing the acceptability of (i) our intensive VRCET as a stand-alone (after 2 weeks of treatment; V1) or add-on (post-treatment; V2; VRCET +) intervention and (ii) VRE as a cue-exposure paradigm, for each new VRE performed in therapy.The Spatial Presence for Immersive Environments (SPIE) – Cybersickness subscale mean total scores will be used to subjectively assess acceptable cybersickness symptoms (i.e., < 7) experienced by participants exposed to VRCE; items range from 0 (“strongly disagree”) to 10 (“strongly agree”; [62]).The Client Satisfaction Questionnaire – 8 (CSQ-8) mean total scores will be used to subjectively assess satisfaction levels towards psychotherapeutic services (≥ 21; “good”); items range from 8 to 32 [63].

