## Statistical methods

### Statistical methods for primary and secondary outcomes {20a}

Statistical analyses for principal and secondary outcome will be computed from self-report scales raw total scores or physiological signals (i.e., blood pressure, skin temperature and conductance) using, respectively, R Statistical [66] and OpenSignals (© PLUX S.A.) software. Our comprehensive data working R code, including R packages and inferential statistical hypothesis testing assumptions (Gaussian distribution, homoscedasticity, etc.), will be made available. For each primary or secondary variable of interest, descriptive statistics (n, min, max, median, q1, q3, iqr, mean, sd, se, and mean ci) will be computed using the *rstatix R* package. Primary inferential statistical analyses will consist of two-tailored independent *t*-tests on score changes between T0 (baseline) and T2 (post-treatment) in the experimental (i.e., VRCET +), compared with the active control therapeutic arm (PCET). In case of mostly non-normal variable distributions but symmetrical score differences around the median, Friedman and Bonferroni-corrected Wilcoxon signed-rank tests will be performed to test and contrast score differences between the conditions using *stats* and *rstatix R* packages [67]. In case of non-symmetrical paired score differences, Bonferroni-corrected Sign tests will be performed. Causal mediation analyses will be adjusted for confounding factors. Cohen’s d, Kendall’s W, and Cliff’s delta effect sizes for score changes across treatment arms (“negligible,” “small,” “medium,” and “large” effect for Cliff’s d inferior to 0.15, 0.33, 0.47, and superior to 0.47; [68]) with 95% CIs will be computed using *irr* and *effsize R* packages.

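### Craving frequency (CEQ-F) is named as a mediator of the craving reduction although it is one of the two primary craving scores, and neither subscale nor visit separates mediator from outcome.

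*Protocol article*

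**What the plan says.** Outcomes {12} of the protocol article defines the primary outcome: "Our primary outcome will consist in the decrease of the self-reported cocaine craving as assessed with the French Craving Experience Questionnaire". It adds "Means of CEQ-S and CEQ-F total scores will be analyzed", so both subscales are primary scores. CEQ-S is taken straight after a 7-minute virtual reality exposure. CEQ-F looks back over 14 days.

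The secondary outcomes in the same section include the "factors (cocaine craving, dysfunctional thoughts, cocaine use, and emotional dysregulation) mediating the efficacy of VRCET+ in decreasing self-reported cocaine craving". The instruments follow: "The CEQ – F, QCBDU, TLFB, and DERS mean total scores will be used to subjectively assess" these factors, with CEQ-F assigned to craving frequency.

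Objectives {7} gives a longer mediator list: "cocaine craving, self-efficacy to cope with craving, dysfunctional thoughts, cocaine use and emotional dysregulation) mediating the efficacy of VRCET". Craving is again both a mediator and the thing to be explained. Self-efficacy appears here but not in the Outcomes list.

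On method, Statistical methods {20a} says only: "Causal mediation analyses will be adjusted for confounding factors". The article does not limit the mediation outcome to CEQ-S, and it does not place the mediator at an earlier visit than the outcome.

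**The concern.** A mediation analysis asks whether treatment changes something else that in turn changes the outcome. Here one named mediator is part of the outcome. Read literally, the plan allows craving to explain the reduction in craving, which says nothing about mechanism. Even with CEQ-S as the outcome, two subscales of one questionnaire completed at the same visit are likely to be correlated because they measure the same construct by self-report. A mediation model reads that correlation as an indirect effect whenever both scores shift with treatment. Adjustment for measured confounders does not reliably remove it.

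At stake is the secondary objective on what carries the effect of VRCET+. A substantial and significant indirect effect through CEQ-F could be reported although the data contain no causal path from CEQ-F to CEQ-S.

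**Working it through.** The article states no mediated share, so there is no figure to reproduce. The check works out what the stated analysis would return.

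**Inputs from the article.** There are 54 participants at 1:1, so 27 per arm. The primary contrast is change from T0 to T2. T1 is at session 11 and T2 at session 15, with sessions Monday to Friday. CEQ-F recall is 14 days and TLFB recall 21 days.

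**Assumed.** The within-arm correlation r between mediator and outcome, and the standardised arm effects d_M (mediator) and d_Y (outcome). The article speaks of a large effect without a number. The values 0.5 to 1.0 are used, plus d_M = 0.

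**Formula.** With T the arm, M = d_M·T + e_M and Y = d_Y·T + e_Y, unit variances, corr(e_M, e_Y) = r, and no effect of M on Y:
- regression of M on T gives a = d_M;
- regression of Y on T and M gives b = r;
- the total effect is c = d_Y;
- apparent mediated share = a·b/c = r × d_M/d_Y.

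**Case 1: CEQ-F as mediator and outcome, same visit.** M = Y, so b = 1 and the direct effect is 0. The share is 100%. This is an identity and not a finding.

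**Case 2: CEQ-F as mediator, CEQ-S as outcome, same visit, no causal path.**

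| d_M, d_Y | r = 0.3 | r = 0.5 | r = 0.7 | r = 0.9 |
|---|---|---|---|---|
| 1.0, 1.0 (any equal pair) | 30% | 50% | 70% | 90% |
| 0.5, 1.0 | 15% | 25% | 35% | 45% |
| 0, 1.0 | 0% | 0% | 0% | 0% |

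Simulation with 27 per arm and 1,500 runs per cell agrees with the formula: 30%, 50% and 71% at r = 0.3, 0.5 and 0.7 with both effects 1.0. Both paths were jointly significant at 0.05 in 59%, 92% and 96% of those trials. With both effects 0.8 the figures were 48%, 78% and 83%. With d_M = 0 they were 3% to 6% at the same correlations.

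**Case 3: a T1 mediator with CEQ-F at T2 as outcome.** Count the first session (a Monday) as day 1. Session 11 is then day 15 and session 15 is day 19, four days later. The CEQ-F recall at T2 covers about days 5 to 18, of which days 5 to 14 precede T1: 10 of 14 days (71%). If the assessment day itself is counted, it is 9 of 14. Most of this outcome therefore lies before the T1 mediator is measured. CEQ-S has no such window, because it is taken after an exposure at the visit.

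**Case 4: T2 mediators with T3 outcomes.** T3 is one month after treatment ends, so its 14-day recall lies wholly after T2.

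**TLFB as a T1 mediator.** The article uses it to "assess participants cocaine abstinence in within the last 21 days". At day 15 this covers days -6 to 14. Days -6 to 0 are seven days before the first session: 7/21 = 33%.

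**Mediator lists.** Objectives {7} has five factors and Outcomes {12} has four, without self-efficacy. Table 4 schedules the DTCQ-8, the self-efficacy measure, at T0, T1, T2 and T3, so the omission is not forced by data collection.

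**The case against.** A reader might infer that the mediated share is large by construction, and that the mechanism question would be answered through craving in every case. The article does not support that. The 100% identity needs CEQ-F in both roles at one visit, a degenerate model that the article nowhere specifies and that few analysts would fit. The description of the mediator as craving frequency over 14 days suits a path from CEQ-F to CEQ-S, and CEQ-S is taken in a different setting. For that path the share runs from 0% to 90% over the assumed inputs. This objection stands and limits the claim.

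It is also true that r × d_M/d_Y applies to any self-report mediator that shifts with treatment and correlates with craving, including QCBDU, DERS and DTCQ-8. What sets CEQ-F apart is that it belongs to the outcome instrument and is itself a primary score. Measuring mediators earlier improves the time order but does not remove unmeasured confounding.

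Visit pairing may be left to an analysis plan, and its absence alone would be no finding. The article does, however, state the mediator, its instrument and the outcome construct, and these overlap. An analysis plan that followed the text would carry the overlap forward.

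The TLFB window matters only if TLFB at T1 is used as a mediator, which the article does not say. Both arms share those pre-treatment days, so the expected effect is dilution.

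A reader might also infer that the result is meant as evidence for habituation. The Discussion rests that inference on the comparison of the two exposure therapies and not on mediation.

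**Conclusion.** The point holds in limited form. CEQ-F is named as mediator of an outcome that includes CEQ-F, and the text does not keep the two apart. Same-visit use of CEQ-F for CEQ-F gives 100% by identity. Same-visit use for CEQ-S can give an apparent share of 30% to 70% with no causal path, if the correlation is 0.3 to 0.7 and the arm effects are equal. The share is smaller if CEQ-F moves less than CEQ-S, and 0% if CEQ-F does not move. The correlations and effects are assumptions. The documents give none.

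Self-efficacy is a mediator in Objectives {7} but not in Outcomes {12}, a plain inconsistency. The consequence is confined to one secondary objective. The primary comparison of T0 to T2 change is unaffected.

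**What to change.** Amend the mediation wording in Objectives {7} and Outcomes {12} as follows:
- Do not use CEQ-F as a mediator when CEQ-F is the outcome, nor as a same-visit mediator of CEQ-S. An earlier CEQ-F with a later CEQ-S could be kept if prespecified, but it would show only that earlier craving relates to later craving.
- Use mediators measured before the outcome (QCBDU, DERS, TLFB, DTCQ-8), adjusted for the T0 mediator and T0 CEQ: T1 values for CEQ-S at T2, and T2 values for CEQ-S and CEQ-F at T3.
- Do not pair T1 mediators with CEQ-F at T2, because about 10 of its 14 recall days precede T1.
- If TLFB serves as a T1 mediator, score only the days since the first session.
- Make the two mediator lists agree on self-efficacy.

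Table 4 already schedules every measure, so this changes wording and analysis code only. The cost is scope. T1 precedes the MFCT week, so T1 mediators speak only to the VRCET phase. Mechanisms of the full package can be examined only against T3, and CEQ-F at T2 has no suitable mediator.

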##### Non-inclusion criteria

If the patients meet any of the following criteria at the screening visit, they will not be eligible for the study:Patient in current high suicidal risk, post-traumatic stress, psychotic, mania, or hypomania episode according to their M.I.N.I.5. score (DSM-IV; [43])Spatial Presence in Immersive Environments – Cybersickness score indicating cybersickness symptoms using VR (≥ 7), as assessed during a tutorial VRE task at inclusion visit [44]Patient with current medical condition (e.g., cardiac or blindness) at risk for safety or compliance in protocol, as assessed by one of the investigator physiciansPatient care under constraint or patient deprived of freedom because of a judicial measurePatient who does not speak and read French

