The exposure in VRET will be habituation-focused, i.e., aiming to reduce the craving response to cocaine-related cues after its repeated, prolonged, and non-reinforced stimulation [47, 48]. To isolate the specific effect of virtual reality on this plausible desensitization mechanism underlying cue-exposure extinction, no other concurrent cognitive, behavioral, or emotional intervention (e.g., relaxation) will be delivered during VRE to cocaine-related cues. In addition, several methodological recommendations arising from meta-analysis of CET for SUDs will be applied to optimize our CET design [15]. First, in order to prevent post-treatment spontaneous craving recovery, i.e., the re-emerging of the extinguished craving response following passage of time between extinction to re-exposure to the cocaine-related cues, VR cue-exposures (VRCE) will be repeated and spaced both between and intra-VRCET sessions [15]. The VRCET phase will consist in a total of 40 repeated 10-min virtual reality exposures (VRE) to cocaine-related cues spread out on 10 daily VRCET sessions. Each VRCET session will consist of 4 VRCE with 2 different VRCET cocaine-related environments per session. Importantly, VRCE to the same cocaine-related environments will be spaced intra (30 min) and between (48 h) VRCE sessions. Secondly, in order to generalize the habituated response to the cocaine-related cues to contexts other than the treatment setting, and to prevent any renew of extinguished cue reactivity, VRCET will be conducted in multiple and various virtual cocaine-related contexts [23, 49]. To do so, participants will be exposed to an increasing and progressive hierarchy of 5 different standard virtual cocaine-related situations, ordered according to the craving level anticipated by the participant for each situation. All the virtual cocaine-related situations will occur in a typical Martinican surrounding and housing (Fig. 3). Exposures to both proximal and distal cocaine-related cues will occur based on the following scenario: peers talk about cocaine (situation 1; Fig. 4) while using it (situation 2; Fig. 5), then the participant gets offered cocaine and virtually holds cocaine as well as its related paraphernalia (e.g., steel spoon, paper tubes, glass pipes, or syringes; situation 3; Fig. 6), thus prepares (situation 4; Fig. 7) and self-administrates (i.e., snorting, smoking or injecting; situation 5; Fig. 8) cocaine doses placed in front of him while seated at a table. For acceptability reasons, participants will switch to another VRCET environment once the self-reported cocaine craving level decreases by 50% for 5 continuous VRCE min (must be ≤ 3/10; 0 = none; 10 = very high).

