
### Participant timeline {13}

#### Inclusion visit (V0)

Every patient treated for CUD at one of the two investigations centers and deemed potentially eligible for study inclusion will be informed by their assigned psychiatrist about the study’s objectives, protocol implications, and expected therapeutic benefits. Each patient will be invited to the inclusion visit (V0) during which the necessary information for giving informed consent to participate will be provided. The dates of the written consent as well as its withdrawn (if applicable) will be documented in their medical record. During this inclusion visit, the research psychiatrist or psychologist will oversee the examination of study eligibility for patients (e.g., Significant SCID-5 CV score for CUD; URICA self-questionnaire score ≥ 11; Non-significant M.I.N.I.5. (DSM-IV) score for current high suicidal risk, post-traumatic stress, psychotic, mania or hypomania episode; Post-VRE SPIE—Cybersickness score ≥ 7).

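### In-therapy cybersickness below 7 is summarised by mean scores, although 7 is a per-patient cut-off; the planned statistics do not give the number of patients who reach it

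*Protocol article*

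**What the plan says.** The fourth secondary objective (Objectives {7}) includes the acceptability of "VRE, as a cue-exposure paradigm via cybersickness self-reported measures".

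Outcomes {12} turns this into a measure: "Cybersickness subscale mean total scores will be used to subjectively assess acceptable cybersickness symptoms (i.e., < 7) experienced by participants exposed to VRCE". The printed range of the scale is 0 to 10. The same section says that the measure concerns "VRE as a cue-exposure paradigm, for each new VRE performed in therapy", and the Intervention description {11a} says that "participants will be exposed to an increasing and progressive hierarchy of 5 different standard virtual cocaine-related situations". A patient in the experimental arm can therefore contribute several scores.

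The value 7 also appears as a criterion for one patient. The Non-inclusion criteria rule out a patient with a "Cybersickness score indicating cybersickness symptoms using VR (≥ 7), as assessed during a tutorial VRE task at inclusion visit". The Inclusion visit (V0) section repeats the number among its eligibility checks ("Post-VRE SPIE—Cybersickness score ≥ 7"). The sign there runs opposite to what one would expect of an eligibility condition, but the number is the same and is applied to one patient.

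Statistical methods {20a} adds that, for each primary or secondary variable, "descriptive statistics (n, min, max, median, q1, q3, iqr, mean, sd, se, and mean ci) will be computed". No section names a count or proportion of patients at or above 7 during therapy.

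**The concern.** The tolerability question is how many patients exposed to VR in therapy reach the level that the protocol itself treats as symptomatic. The stated summary is a mean, and a mean does not answer a question about a per-patient limit.

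Screening weakens the mean further. Patients at or above 7 after the tutorial never enter, so the group starts below the limit. A mean under 7 in therapy is then easily reached and carries little information.

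At stake is how the acceptability objective is read. The reported summary could look comfortable while a reader cannot tell how many patients reached a score that would have excluded them at the tutorial.

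**Working it through.** The value 7 is a criterion, not a calculated figure, so there is no result of the plan to reproduce. The check is whether the planned statistics fix the number of patients at or above 7.

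**Inputs.** From the protocol: 54 patients randomised 1:1, a score range of 0 to 10, and a cut-off of 7. Assumptions: 54 / 2 = 27 patients in the VRCET+ arm before dropout, integer scores, and one score per patient for simplicity. The document gives no mean or SD for this scale, so the data sets below are constructed and are not forecasts.

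**Two data sets with identical planned statistics**

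| Score | 0 | 1 | 2 | 3 | 4 | 5 | 6 | 7 | 8 |
|---|---|---|---|---|---|---|---|---|---|
| Set A, patients | 6 | 0 | 7 | 1 | 1 | 6 | 5 | 0 | 1 |
| Set B, patients | 3 | 2 | 8 | 6 | 0 | 2 | 0 | 5 | 1 |

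- Sum, A: 14 + 3 + 4 + 30 + 30 + 8 = 89. B: 2 + 16 + 18 + 10 + 35 + 8 = 89. Mean = 89 / 27 = 3.30 in both.
- Sum of squares, A: 28 + 9 + 16 + 150 + 180 + 64 = 447. B: 2 + 32 + 54 + 50 + 245 + 64 = 447.
- SD = √[(447 − 89²/27) / 26] = 2.43; SE = 2.43 / √27 = 0.47; 95% CI of the mean 2.33 to 4.26 in both.
- Minimum 0 and maximum 8 in both. The 14th sorted value (median) is 3. The 7th and 8th are both 2 and the 20th and 21st are both 5, so q1 = 2, q3 = 5 and IQR = 3 under the usual quartile definitions.
- Patients at or above 7: A 1/27 = 3.7%; B 6/27 = 22.2%.

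Every statistic listed in {20a} agrees, yet the count differs. Most of the difference is five patients at 6 against five at 7. The pair shows only that the count cannot be recovered, not that such data are likely.

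**What the planned statistics do tell.** With maximum 8 and q3 = 5, at least 1 patient is at or above 7. If q3 is the average of the 20th and 21st values, at most 7 of 27 can be. The count is bounded but not given.

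**How far a mean below 7 can be from reassurance.** As an illustration, assume a beta distribution scaled to 0–10 with an SD between 2 and 3. The expected share at or above 7 is then 4–15% at a mean of 3, 8–21% at a mean of 4, and 18–31% at a mean of 5. All of these means lie well below 7.

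**The case against.** The strongest reply is that the article contains no faulty rule. Mean total scores are the formula used for nearly every scale in Outcomes {12}. The bracketed limit may simply label what counts as acceptable for a participant, much as a score of 21 or more is labelled good for the satisfaction questionnaire. Descriptives beyond the mean are planned, and a count at a cut-off is the sort of detail that an analysis plan or table shell often supplies. Much of this stands, and it rules out three stronger readings that a reader might infer:

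- *That VR exposure will be declared acceptable if the group mean is below 7.* No such rule is written.
- *That a patient's bad exposure will be averaged away.* Scores of 8, 3, 3, 3, 3 do average 4.0, but the article plans no averaging across one patient's exposures.
- *That most patients could exceed the limit unnoticed.* With 22 of 27 at 8 and 5 at 2 the mean is (176 + 10) / 27 = 6.89. However, q1, median and q3 would all be 8, so the planned descriptives would expose it.

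It is also fair that screening lowers the proportion at or above 7 as well as the mean. The proportion, though, still counts the patients who cross the limit.

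The reply does not dispose of the point. The article does more than leave a detail open: it names the summary and the limit together, and that summary does not fit a limit defined elsewhere for one patient. The per-participant reading is plausible, but it is not written.

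**Conclusion.** The point holds in a limited form. Mean scores are a poor summary of whether in-therapy cybersickness stays below a per-patient limit, the more so because patients at that limit are screened out beforehand. The maximum and quartiles soften this by showing whether anyone reached 7 and bounding how many, but the number itself is not among the planned statistics. In the constructed pair it is 1 or 6 of 27 with everything else equal.

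The sizes rest on 27 patients, integer scores and invented distributions. The conclusion that the listed statistics do not determine the count needs only one such pair. The point is minor and concerns a descriptive secondary outcome. The primary craving comparison is not touched.

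**What to change.** In Outcomes {12}, state that the limit of 7 applies per participant. Report the number and proportion of patients who started VRCET and had any in-therapy SPIE-Cybersickness score of 7 or more, with an exact (Clopper-Pearson) 95% CI. Keep the mean as description. A pre-stated maximum acceptable share is optional and for the sponsor to decide.

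The cost is one sentence and one table row, from scores already collected. There are two drawbacks:

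- **Precision is low.** With 27 patients, 0/27 gives 0 to 12.8%, 3/27 gives 2.4% to 29.2%, and 6/27 gives 8.6% to 42.3%.
- **Any score over repeated exposures is stricter than the single tutorial score.** Suppose 5% of single scores reach 7 and each of the five situations is scored once. The share with any such score then lies between 5% (the same patients each time) and 1 − 0.95⁵ = 22.6% (independent scores). The figure may look less favourable than the mean and should be presented with that explanation.
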